##### Power calculations

For each individual patient, the percent of applicable recommendations that were followed will be calculated. Previous studies have seen rates between approximately 30% and 70% of individual recommendations being followed (e.g., colorectal cancer screening). Hence, we assume that the range for a vast majority of possible percentages lie between 20 and 80%, giving approximately a standard deviation of 15% (based on the Empirical Rule at with 95% of all observations falling within four standard deviations). Assuming this standard deviation, an interclass correlation of 0.1 [88], a dropout rate for practices of approximately 15%, and a mean difference in percentages between control and intervention practices of 15%, we would require 26 practices to achieve 90% power when conducting the test at the 0.05 level accounting for clustering within practice. If the interclass correlation was higher, say at 0.3, we would need to see a difference of 13% to achieve the same power with 26 practices.

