### Patient-level outcome variables

The primary outcome variable will be breast cancer comprehensive follow-up care. This will be assessed by calculating the percentage of recommendations followed out of the total recommendations a given person is eligible to receive. Lower scores will indicate less comprehensive care. The number of recommendations may vary by patient depending on personal characteristics, like weight or smoking status. Research staff will collect data from the Electronic Health Record (EHR), conducting chart abstractions on 20 randomly selected patient records per practice at each time point. Measures of care coordination/management will be assessed from chart documentation of referral and/or treatment and screening for late and long-term effects, lifestyle, surveillance, and screening activities.

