#### Quantitative analysis

The primary outcome for each patient will be the percent of recommendations followed out of those for which the patient was eligible. Descriptive statistics and visualization techniques will summarize the practice averages of these percentages, overall and by treatment group and time. Additionally, we will calculate the practice rates of providing each individual service from patients for whom the service was appropriate and compare these across treatment arms and times. In formal analyses, hierarchical linear models we will study the effect of treatment on the primary outcome. Specifically, the model will include a random effect for practice to account for intra-practice correlation between patients, effects for time (baseline/follow-up) and intervention group (intervention/control), and patient characteristics such as age, race, count of co-morbidities. To test whether the intervention affects changes in the outcome over time, we will use an F-test of the interaction between treatment arm and time. In exploratory analyses, hierarchical logistic models will examine effects of the intervention on changes over time on rates of fulfillment of individual services.

Since practices in this study will be chosen for their diversity in patient population and management systems, analyses will also be conducted separately for each practice. These analyses will allow us to qualitatively examine characteristics of practices in which the intervention was effective versus those where it was not.

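### The power figures do not follow from the documented design: at 20 charts per practice, 26 practices detect about 8 points at ICC 0.1, not 15, and the larger ICC is paired with the smaller difference

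*Protocol article*

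**What the plan says.** The Power calculations section derives its SD from an assumed range of 20% to 80%, "giving approximately a standard deviation of 15" percentage points. It adds "an interclass correlation of 0.1" and "a dropout rate for practices of approximately 15" percent, and states that with "a mean difference in percentages between control and intervention practices of 15%, we would require 26 practices to achieve 90% power" at the 0.05 level, allowing for clustering. It closes with the alternative scenario: "If the interclass correlation was higher, say at 0.3, we would need to see a difference of 13% to achieve the same power", again with 26 practices.

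The section gives no cluster size. The Patient-level outcome variables section does: "conducting chart abstractions on 20 randomly selected patient records per practice at each time point". Participants and procedures gives 13 intervention and 13 waitlist practices, randomized in pairs. The Quantitative analysis section names the test. In a hierarchical linear model with a random practice effect, "we will use an F-test of the interaction between treatment arm and time".

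**The concern.** The second scenario is introduced as the harder one, because the ICC is higher, yet it is given the smaller detectable difference. For the quantity that the paragraph names, a mean difference between arms, that is the wrong direction. The paragraph also sizes a difference between arms while the planned test is on a difference in change.

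This paragraph is the article's only statement of what effect the trial can detect. If the base-case figure is wrong, the stated basis for 26 practices falls, and a reader could take 15 points as the limit of the design when the limit is nearer 8.

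**Working it through.** **Inputs.** From Power calculations: SD 15, ICC 0.1 or 0.3, practice dropout 15%, power 90%, level 0.05. From Patient-level outcome variables: m = 20 charts per practice per time point. From Participants and procedures: 13 practices per arm. Assumed: a two-sided test, and fresh charts at each time point. After dropout, 26 × 0.85 = 22.1, so k = 11 practices per arm.

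**The plan's SD.** (80 − 20)/4 = 15. This reproduces.

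**Between-arm comparison.** SE = sqrt(2 × 15² × (1 + (m − 1) × ICC)/(m × k)). The design effect is 1 + 19 × 0.1 = 2.9, or 1 + 19 × 0.3 = 6.7.

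- ICC 0.1: SE = sqrt(450 × 2.9/220) = 2.44.
- ICC 0.3: SE = sqrt(450 × 6.7/220) = 3.70.

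By the noncentral t with 2(k − 1) = 20 df, 90% power needs a difference of about 3.41 SE. The detectable differences are **8.3** points (ICC 0.1) and **12.6** points (ICC 0.3).

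- 13 points at ICC 0.3: power is 91.6% with 11 per arm, and 22/0.85 = 25.9, so 26 practices. The second sentence reproduces.
- 15 points at ICC 0.1: power is above 99.9% with 11 per arm. Four per arm give 87% and five give 95%, so 10 practices, and 10/0.85 = 11.8, or 12 with dropout. The first sentence does not reproduce.
- If 15 were right at ICC 0.1, the figure at ICC 0.3 would be 15 × sqrt(6.7/2.9) = 22.8, not 13.

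The design effect rises with the ICC for every m above 1 and is flat at m = 1, so no cluster size gives 15 and then 13 for this comparison.

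Variants at ICC 0.1 and 0.3:

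| Variant | ICC 0.1 | ICC 0.3 |
|---|---|---|
| All 13 per arm | 7.6 | 11.5 |
| 11 per arm, matched-pair df | 8.8 | 13.3 |
| 11 per arm, one-sided | 7.4 | 11.2 |

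**Arm-by-time test.** Let r be the correlation of a practice's effect between baseline and follow-up. The variance of a practice's change is 2 × 15² × ((1 − ICC)/m + ICC × (1 − r)), and SE = sqrt(2 × that/k). With m = 20 and k = 11:

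| r | Detectable, ICC 0.1 | Detectable, ICC 0.3 | Practices for 15 points at ICC 0.1, with dropout |
|---|---|---|---|
| 1 | 6.5 | 5.8 | 10 |
| 0.8 | 7.9 | 9.5 | 10 |
| 0.5 | 9.5 | 13.3 | 15 |
| 0 | 11.7 | 17.9 | 19 (22 with matched-pair df) |

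The detectable difference falls as the ICC rises only when r exceeds 1 − 1/m, which is 0.95 at m = 20. For example, r = 0.97 gives 6.76 and 6.47.

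**Can this test give 15 and 13?** At r = 1 the detectable change scales with sqrt(1 − ICC), and 15 × sqrt(0.7/0.9) = 13.2, so the ratio fits. For the size, m = 4 gives SE = sqrt(4 × 225 × 0.9/44) = 4.29 and sqrt(4 × 225 × 0.7/44) = 3.78, hence 14.6 and 12.9 points. Both stated figures are therefore approached at about 4 charts per practice per period, against the documented 20.

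**The case against.** The strongest defence is that the order, 15 and then 13, is what the plan's own model produces. Quantitative analysis specifies one random practice effect and an arm-by-time test. In that model stable practice differences cancel, so a higher ICC leaves less residual variance and a smaller detectable change. Power calculations states no cluster size, and about 4 charts would bring both figures close. On this view the two sentences need not contradict each other under every test, and the fault is a mismatch with the 20 charts. That stands as a possible account of where the figures came from. It does not rescue the paragraph, which names a mean difference between arms, and at 20 charts the change test gives 6.5 and 5.8.

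A reader might also infer that 26 practices are far more than 15 points needs. That is clear for the between-arm comparison (12 against 26). The excess shrinks for the planned test as r falls: 15 practices at r = 0.5, and 19 to 22 at r = 0. No variant tried with 20 charts at ICC 0.1 reaches 26, but the size of the excess depends on r, which the article does not give.

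Finally, it can be said that the result will be judged on its estimate and test, so that misreading the design's sensitivity is only a risk. That is fair. It bears on the consequences, not on whether the figures are right.

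**Conclusion.** Wrong as written. For the comparison that the paragraph names, 15 points at ICC 0.1 and 13 points at ICC 0.3 cannot both hold with the same 26 practices and power. At 20 charts per practice and 22 analysable practices the figures are about 8.3 and 12.6. The ICC 0.3 figure stands; the base-case figure is overstated nearly twofold (15/8.3 = 1.8), and 26 practices do not follow from it. Reading the paragraph as the arm-by-time test explains the order but not the size, unless about 4 charts per period were assumed, which conflicts with Patient-level outcome variables.

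A reader might infer from a faulty power statement that the trial is too small. The documents do not support that. At the base-case ICC of 0.1, 22 practices give at least 98.5% power for 15 points on the arm-by-time test, even with no over-time correlation of practice effects.

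The conclusion rests on a two-sided test, on 20 as the cluster size and on fresh chart samples. One-sided testing, matched-pair degrees of freedom or keeping all 26 practices changes the between-arm figures by about a point or less at ICC 0.1, and by no more than about 1.4 points at ICC 0.3.

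**What to change.** Recompute and restate the paragraph:

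- Give the cluster size (20 charts per practice per time point), the 22 analysable practices, the sidedness of the test and the contrast used. If a smaller cluster size was used, say so and reconcile it with the 20 charts.
- For the between-arm comparison, give about 8 points at ICC 0.1 and about 13 at ICC 0.3.
- Add the detectable difference for the planned arm-by-time test under a stated over-time correlation of practice effects. At ICC 0.1 it is 6.5, 7.9 and 9.5 points for correlations of 1, 0.8 and 0.5.
- Remove the statement that 15 points at ICC 0.1 requires 26 practices.

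The cost is one recalculation and one paragraph. Enrolment does not change.

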## Discussion

This study is innovative in several key ways. First, its comprehensive focus on primary care delivery to patients with a history of breast cancer addresses the lack of care continuity for these patients. While limited studies have evaluated the impact of SCPs [40] and models of care for integrating primary care into breast cancer follow-up [89], we are not aware of any systematic studies that have used implementation science theoretical frameworks to holistically understand the inner (primary care) and outer (oncology and broader cancer policy) contextual factors that impact implementation of breast cancer care. Second, we use an innovative multi-level approach that combines two established frameworks— Exploration, Planning, Implementation, and Sustainment (EPIS) and the Practice Change Model—to simultaneously explore health system, practice, clinician, and patient-level factors that impact implementation of care for patients with a history of breast cancer. Third, we simultaneously engage different and disparate stakeholders (national experts and local implementers from oncology, primary care, nursing, social work, and patients) using mixed methods to triangulate data and gain a comprehensive understanding of multiple perspectives on delivery of breast cancer care in primary care settings. While there is literature that addresses different stakeholders, particularly clinicians [90, 91] and patients [92, 93], there is a significant gap in research that incorporates other perspectives. Finally, multiple professional organizations advocate clinical recommendations and guidelines for primary care; however, this will be the first time where all of these will be considered simultaneously, prioritized, and synthesized into actionable plans for providing care to long-term breast cancer patients in primary care settings.

Study findings are poised to inform development of scalable, high impact intervention processes in primary care to enhance long-term follow-up care for patients with a history of breast cancer. If successful, next steps would include working with a national primary care practice-based research network to implement a national dissemination study. Actionable activities and processes identified could also be applied to development of organizational and care delivery interventions for follow-up care for other cancer sites.

## Data Availability

The datasets generated and/or analyzed during the current study will not be publicly available due to privacy concerns.
